##### Lipid profile

Lipid profile parameters to be measured in this trial include TG, TC, LDL-C and HDL-C, and TC:HDL-C ratio. These parameters will be measured in blood samples obtained from participants at baseline and post-intervention visits by HNEHAPS.

##### Inflammatory parameters

Inflammation-related parameters, such as IL-6, IL-1β, adiponectin and leptin in blood samples of participants at baseline and post-intervention visits, will be measured using human antibody-specific Enzyme-Linked Immunosorbent Assay (ELISA) kits (R&D Systems) at our laboratory in NRG; while the other two parameters, CRP and whole blood cell count, will be analysed by HNEHAPS.

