Subclinical inflammation, being the primary trigger for many pathological mechanisms in the development of T2D, anti-inflammatory bioactives, such as curcumin and long-chain omega-3 polyunsaturated fatty acids (LCn-3PUFA), appear to be an attractive strategy to delay the risk of developing T2D in individuals with prediabetes. These bioactive compounds influence multiple numbers of physiological mechanisms and have relatively higher safety profiles [22, 23]. These bioactives could provide beneficial effects in insulin resistance and T2D by the following pathways: (1) down-regulating inhibitor of kappa B kinase (IKK)/nuclear factor kappa B (NFκB), and c-Jun N-terminal kinase (JNK) pathways for lowering chronic low-grade inflammation, (2) scavenging reactive oxygen species (ROS) and reducing oxidative stress, (3) providing cytoprotection for improving beta-cell function, (4) reducing the accumulation of fatty acid metabolites for increasing insulin sensitivity, (5) up-regulation of 5' AMP-activated protein kinase (AMPK), and (6) modulating peroxisome proliferator-activated receptor gamma (PPARγ) agonistic activity.

Some preclinical studies have reported synergistic anti-inflammatory effects of curcumin and docosahexaenoic acid (DHA) combination. These observations suggest that curcumin might provide synergistic anti-inflammatory effects with LCn-3PUFA in the prevention of T2D [24–26]. In this study we aim to perform a 2 × 2 factorial, double-blinded, randomised placebo-controlled trial to evaluate the complimentary or synergistic effects of curcumin and/or LCn-3PUFA primarily on glycaemic profiles and in individuals with prediabetes (IFG, IGT or both). In addition to these parameters we are also measuring lipid profile and inflammatory parameters to determine the effects of curcumin and/or LCn-3PUFA on cardiovascular risk factors and chronic low-grade inflammation.

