### Sample size calculation

Based on the HbA1c data of the prediabetic people from other studies [27, 28], with a standard deviation of 0.5 units in HbA1c, a sample size of 17 participants in each treatment group will give 80% power to detect a 0.5-unit fall in HbA1c at a type 1 error (alpha) of 0.05. To allow for dropouts we will recruit 4 × 20 = 80 participants according to the inclusion criteria.

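### The inflammatory secondary outcomes have no stated safeguard against acute illness at the single baseline and week-12 draws, and the stated analysis would turn a few acute values into a large loss of precision

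*Protocol article*

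**What the plan says.** All references are to the protocol article.

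- **Purpose.** The Background says the additional markers are there "to determine the effects of curcumin and/or LCn-3PUFA on cardiovascular risk factors and chronic low-grade inflammation".
- **Markers.** The section Inflammatory parameters lists "Inflammation-related parameters, such as IL-6, IL-1β, adiponectin and leptin in blood samples of participants at baseline and post-intervention visits", measured in the trial's own laboratory, "while the other two parameters, CRP and whole blood cell count, will be analysed by HNEHAPS". Secondary outcomes places the group among the secondary outcomes.
- **Sampling.** Table 1 shows one blood sample at baseline and one at week 12. Baseline assessments and Post-intervention visit require an overnight fast of 10 hours and state no other condition for the draw. The final visit is scheduled for the last day of the intervention.
- **Exclusions.** The list goes down to individual drugs, but it names neither acute infection nor inflammatory disease.
- **Analysis.** Data analysis takes all participants under intention to treat. It examines the normality of baseline data, then uses ANOVA if the data are normal and the Wilcoxon signed rank test if they are not. The effects of the two supplements come from a two-way ANOVA. ANCOVA covariates are age, gender, BMI, physical activity and diet. No transformation is mentioned, and neither the baseline marker value nor illness is a covariate.

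**The concern.** CRP, IL-6, IL-1β and the blood cell count respond to acute infection as well as to the slow subclinical process that the trial wants to measure. An acute value can be many times the chronic level. With one draw per time point there is no repeat to average it out, and a change score carries it in full.

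The stated analysis gives little protection. The choice of test rests on baseline data, so an acute value at week 12 cannot alter it. If the data are judged normal, the value enters an ANOVA of untransformed means. If they are not, the named test is paired and within-group, so it offers no robust comparison between arms.

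At stake is the precision of the outcomes that carry the trial's anti-inflammatory rationale. A real effect on these markers could be missed because a handful of participants had an infection on the day of the draw.

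**Working it through.** **1. The plan's own figure.** The only sample size is for HbA1c: "a sample size of 17 participants in each treatment group will give 80% power to detect a 0.5-unit fall in HbA1c", "with a standard deviation of 0.5 units in HbA1c", "at a type 1 error (alpha) of 0.05".

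- Standardised difference: 0.5 / 0.5 = 1.0.
- Normal approximation, two-sided: n = 2 × (1.96 + 0.84)² / 1.0² = 15.7, so 16 per arm.
- Two-sample t-test: power is 78.1% at 16 per arm and 80.7% at 17.

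The stated 17 is reproduced as the two-sided t-test figure. It was not calculated for the inflammatory markers.

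**2. Sizes used below.** The article says: "To allow for dropouts we will recruit 4 × 20 = 80 participants". Taking 17 completers per arm gives 4 × 17 = 68 completers and 68 × 2 = 136 draws. A factorial main effect pools two arms on each side, 34 v 34. A comparison of two single arms is 17 v 17.

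**3. Chance that illness occurs at all** (illness rates assumed):

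- At 3% per draw: 1 − 0.97^136 = 98%; expected number 136 × 0.03 = 4.1 draws.
- At 1% per draw: 1 − 0.99^136 = 75%; expected number 136 × 0.01 = 1.4 draws.

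This is the chance of at least one ill draw somewhere in the trial. It is not the chance of losing an effect.

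**4. Effect on power.** The documents give no CRP distribution, effect size or illness rate, so every input here is an assumption: lognormal CRP, median 2.5 mg/L, log SD 0.9, within-person correlation 0.7, a true 40% fall, illness striking either visit in any arm at random, and ill values log-uniform between 10 and 80 mg/L. The test is a two-group t-test on change at two-sided 5%, simulated.

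| Contrast | Scale | No illness | 3% of draws ill | 3% ill, those draws set aside |
|---|---|---|---|---|
| Main effect, 34 v 34 | raw | 48% | 14% | 46% |
| Main effect, 34 v 34 | log | 85% | 58% | 82% |
| Two arms, 17 v 17 | raw | 28% | 10% | 27% |
| Two arms, 17 v 17 | log | 54% | 35% | 52% |

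**5. How far this depends on the assumptions.**

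- *Lower illness rate.* At 1% of draws, log-scale power at 17 v 17 falls only from 54% to 47%; at 34 v 34 it falls from 85% to 73%.
- *Milder illness.* With ill values of 10 to 30 mg/L at 3% of draws, 17 v 17 power is 16% raw and 39% log.
- *Different model.* Median 3 mg/L, log SD 0.8, correlation 0.6, a true effect of 1 SD of log change, and exactly one active-arm participant ill at week 12 with 20 to 50 mg/L. At 34 v 34, power goes from 73% to between 32% and 0.2% raw, and from 98% to between 93% and 88% log. At 17 v 17, it goes from 46% to 3% or less raw, and from 81% to between 46% and 29% log.

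**6. False positives.** With no true effect and 3% of draws ill, the 17 v 17 rejection rate is 1.9% raw and 4.4% log. Neither exceeds 5%.

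**The case against.** The strongest objection is that this is a condensed article. A wellness check before the draw, or a rule for outlying assay values, often sits in visit forms, laboratory procedures or an analysis plan that is not shown. A reader might infer that blood is drawn and analysed whether or not the participant is ill. The article does not say so; it is silent. Nor does scheduling the last visit on the final intervention day forbid moving it. That part stands. What remains is that the article does state draw conditions, does itemise exclusions, and does fix how the test is chosen; those stated choices leave the markers exposed.

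Second, a reader might infer that one or two ill participants erase a true effect, or that these outcomes lose most of their power. That holds only for untransformed means. On the log scale, a main effect under the assumptions above keeps 58% of an original 85%. A between-group rank test would keep 73% of 82% at 34 v 34. The article's own normality check might well steer skewed CRP away from raw-scale ANOVA. But the route it then names is a paired test, so the robust between-group comparison is not in the stated plan.

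Third, a reader might infer that a chance cluster of illness would readily pass for a treatment effect. Illness can push a single estimate either way, but the simulated false-positive rate stays below 5%.

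Fourth, some information on illness would exist: a medical questionnaire before baseline, adverse events at weeks 6 and 12, and CRP and cell count from the same blood as the cytokines. This mitigates in part. None of it is tied to sampling or analysis, and Table 1 has no adverse event recording at baseline.

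**Conclusion.** The point holds as one of precision in secondary outcomes. The article aims these markers at chronic inflammation, draws each once per time point with no stated condition on acute illness, and describes an analysis with no robust comparison between arms. Under the assumed 3% illness rate, a factorial main effect loses 48 − 14 = 34 points of power on the raw scale and 85 − 58 = 27 on the log scale. For 17 v 17 the losses are 28 − 10 = 18 and 54 − 35 = 19 points. At 1% illness the 17 v 17 log-scale loss is 54 − 47 = 7 points.

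These sizes rest wholly on assumed CRP values and illness rates and should be read as a range. The direction does not depend on them. The primary outcome, HbA1c, and its sample size are untouched. The remedy is cheap, and because the article reports recruitment as ongoing with 38 participants through all visits, it could still help the remainder.

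**What to change.** 1. At visits 1 and 3, before blood is taken, blinded staff record whether the participant has a current acute infection.
2. If so at visit 1, rebook the visit before randomisation. At visit 3, take the blood and flag the sample.
3. In Data analysis, state that CRP, IL-6, IL-1β and the white-cell count are analysed on the log scale in the between-group factorial model, adjusted for the baseline value of the marker. Do not let baseline normality select a paired test for a between-arm question.
4. Report the all-values analysis. Beside it, show a pre-specified analysis that sets flagged draws aside. Keep both, because setting aside draws after randomisation departs from the full randomised comparison. HbA1c keeps every participant.

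In the working table, moving from raw to log scale raises main-effect power at 3% illness from 14% to 58%, and setting ill draws aside raises it further to 82%. Those figures assume that every ill draw is identified.

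Cost: one question on two visit forms and a short addition to Data analysis. A few baseline visits move by days, and a small share of draws is left out of the second analysis of these secondary outcomes only. Participants who have already completed have no flag, so for them only the log-scale analysis helps.

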### Additional data

#### Body composition

Body weight, BMI, body fat mass, percent body fat, waist-hip ratio and skeletal muscle mass are measured using bioelectric impedance (InBody 230). These parameters are measured in a fasting state at baseline, follow-up and post-intervention visits.

#### Questionnaires

Changes in the dietary pattern, such as an increase in turmeric or fatty fish intake during the trial period, might alter the effects of intervention on clinical outcomes. To avoid this, the participants are advised to maintain a consistent dietary pattern during the trial period. They will be asked to complete a 3-day food record during each visit to enable us to get an appropriate picture of the dietary intake pattern of participants and identify any major changes in the dietary habits of participants. These food diaries will be analysed with Food Works Professional 8 2015 (Xyris software (Australia) Pvt. Ltd.). Along with dietary intake, participants will be advised to maintain similar physical activity during the 12-week trial period. The IPAQ long version is used to assess the levels of physical activity. This version allows the participants to record the number of hours or minutes that they spent on job-related physical activity, travel-related physical activity and recreation- or sport-related physical activity during the last 7 days. It also has a provision for recording the number of days, hours or minutes participant spend on walking and sitting. The physical activity of the participant will be reported in metabolic equivalents (METs)-minutes/week. This will also help us to determine the impact of different levels of physical activity on intervention.

### Data analysis

Data obtained from the all participants will be analysed according to the intention-to-treat principle. In case of missing data or dropouts, pairwise deletion will be used to analyse the significant effect of intervention in participants who have completed the trial. Normality of baseline data will be examined using histograms with a normal distribution curve overlayed and the Shapiro-Wilk test. Based on the distribution of data, the outcome measures will be analysed using analysis of variance (ANOVA) (normal distribution) or the Wilcoxon signed rank test (nonparametric data). Two-way ANOVA with post hoc comparisons (Bonferroni correction) will be used to determine the effect of intervention on different variables and also to determine synergistic and/or complimentary effects between the two interventions (curcumin and LCn-3PUFA). ANCOVA will be used to assess the effects of confounding factors on treatment that include age, gender, BMI, physical activity levels and dietary intake. Significance will be set at a *P* value < 0.05. Statistical analysis will be performed using GraphPad Prism version 6 and IBM SPSS 22 software.

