## Method/design

This is a 12-week 2 × 2 factorial, double-blinded (study investigator and participants), randomised placebo-controlled intervention trial for preventing or delaying the onset of T2D using curcumin and/or fish oil as supplements. Eighty individuals diagnosed with prediabetes (IFG fasting glucose 6.1–6.9 mmol/L; IGT-2 h OGTT plasma glucose ≥7.8 mmol/L and ≤11.1; glycosylated haemoglobin (HbA1c) 5.7–6.5 mmol/L) aged between 30 and 70 years will be screened for enrolment at two sites; Nutraceuticals Research Group (NRG) and John Hunter Hospital (JHH) in Newcastle, NSW, Australia. Potential participants who meet the inclusion and exclusion criteria will be randomised to receive double placebo (corn oil capsules or curcumin placebo tablets), curcumin plus placebo matching for fish oil, fish oil plus placebo matching for curcumin or both curcumin and fish oil. Participants visit the trial sites three times at baseline (0 weeks), interim (6 weeks) and post intervention (12 weeks). Figure 1 shows a flow chart of the study design and the Standard Protocol Items: Recommendations for Interventional Trials (SPIRIT) Checklist is presented as Additional file 1.

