### Inclusion criteria

To be eligible to participate in the trial, participants should be within the age range of 30–70 years. Their Body Mass Index (BMI) must lie between 25 and 45 kg/m^2^. They must be diagnosed either with IFG (fasting glucose 6.1–6.9 mmol/L), IGT (2-h OGTT plasma glucose ≥7.8 mmol/L and <11.1 mmol/L) or both. They can also take part in the trial if their HbA1c levels lie between 5.7 and 6.4% or they obtain a score of 12 or more in the Australian type 2 diabetes risk (AUSDRISK) tool assessment (a noninvasive questionnaire to determine the risk of developing diabetes). The participants should not take part in any clinical trial (particularly with new investigational drugs) before starting this trial. They must be readily available for 3 months and should be willing to maintain similar dietary patterns and physical activity during the trial period.

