### Data collection and outcome measures

#### Primary outcome

The primary outcome measure in this trial is the difference in HbA1c levels in 12 weeks between double placebo, curcumin, LCn-3PUFA and double active groups from baseline to the post-intervention visit (Additional file 2). HbA1c is measured in blood samples obtained at baseline and post-intervention visits through the cation exchange HPLC method by Hunter New England Area Health Pathology Services (HNEHAPS) (accredited pathology laboratory for compliance with National Pathology Accreditation Advisory Council Standards).

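### The choice between ANOVA and the signed rank test hangs on normality of baseline data, which is not what ANOVA assumes, and the fallback test cannot answer the primary question

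*Protocol article*

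**What the plan says.** All of the analysis rules stand in the Data analysis section of the protocol article.

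- The normality check: "Normality of baseline data will be examined using histograms with a normal distribution curve overlayed and the Shapiro-Wilk test". No check of residuals, change scores or week-12 values is named.
- The rule that selects the method: "Based on the distribution of data, the outcome measures will be analysed using analysis of variance (ANOVA) (normal distribution) or the Wilcoxon signed rank test", the latter for nonparametric data.
- The factorial analysis, with no condition attached: "Two-way ANOVA with post hoc comparisons (Bonferroni correction) will be used to determine the effect of intervention on different variables". The same sentence assigns it the question of synergy.
- ANCOVA is listed for age, gender, BMI, physical activity and diet. Baseline HbA1c is not among these covariates.

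The Primary outcome section defines the target as "the difference in HbA1c levels in 12 weeks between double placebo, curcumin, LCn-3PUFA and double active groups from baseline to the post-intervention visit". This is a comparison between groups.

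On eligibility, the Inclusion criteria section admits people with IFG, IGT or both, and then adds a route by HbA1c: "They can also take part in the trial if their HbA1c levels lie between 5.7 and 6.4" percent. A further alternative, by questionnaire score, follows in the same sentence: "or they obtain a score of 12 or more in the Australian type 2 diabetes risk (AUSDRISK) tool assessment". The Method/design section prints the HbA1c range differently, as "glycosylated haemoglobin (HbA1c) 5.7–6.5 mmol/L".

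**The concern.** There are three faults in the rule as written.

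1. **Wrong quantity.** The normality assumption of ANOVA and ANCOVA concerns the errors of the outcome within groups. Baseline values may be far from normal while the errors of the change are exactly normal, and the reverse can also occur. Passing or failing at baseline therefore says little about whether ANOVA is sound.
2. **Wrong fallback.** The signed rank test is a one-sample or paired test. It asks whether values moved within one group. It gives no comparison of four arms, no main effect of curcumin or fish oil, and no interaction. Those are the purpose of the 2 × 2 design.
3. **Unclear precedence.** The choice rule covers all outcome measures, while the two-way ANOVA sentence carries no condition. If HbA1c fails the check, the text does not say which governs, so the primary test is settled only after data have been seen.

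At stake is the primary comparison itself. If within-arm tests replaced the factorial model, a change common to all arms, placebo included, could be read as a treatment effect.

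**Working it through.** **Inputs from the protocol article.** Sample size calculation: SD 0.5, difference 0.5, alpha 0.05, power 80%, 17 per group, 20 recruited per group. Inclusion criteria: HbA1c 5.7–6.4% as one route of several.

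**The plan's own figure.** Per-group n = 2 × (1.96 + 0.84)² × (0.5/0.5)² = 15.7, so 16 by the normal approximation. The two-sample t-test gives 16.7, so 17, with 80.7% power. The stated 17 is reproduced, and this point does not change it. It sets the sizes used below: 4 × 17 = 68 completers, 4 × 20 = 80 recruited, 20 per arm.

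**Step 1. How often would Shapiro-Wilk (0.05 level) reject baseline HbA1c?** This was simulated. The parent distributions are assumptions, because the documents give no baseline distribution.

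| Assumed make-up of baseline HbA1c | N = 80 | N = 68 | n = 20 (one arm) |
|---|---|---|---|
| All inside 5.7–6.4, parent mean 5.9 or 6.05, SD 0.5 | 92–93% | 83–85% | 14–16% |
| All inside, parent mean 6.05, SD 0.2 | 19% | 15% | 4% |
| 25% enter by the window, rest normal (mean 5.6, SD 0.4) | 25% | 21% | 6% |
| 50% by the window, rest as above | 83% | 76% | 21% |
| 75% by the window, rest as above | 96% | 93% | 40% |
| No limit, normal | 4% | 5% | 5% |
| All qualify on an earlier value in the window, baseline re-measured | 4–19% | 4–15% | not run |

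The last row uses parents with mean 6.0, SD 0.5 and mean 5.9, SD 0.3, and a within-person SD of 0.1 to 0.2. Its upper end arises when within-person noise is added only to the new measurement. If the noise affects both measurements, rejection at N = 80 is 4–7%.

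**Step 2. Does a failed baseline check mean that ANOVA is unsound?** In simulated trials with 17 per arm, all baselines were inside the window (parent mean 5.9, SD 0.5), the changes were normal and there was no treatment effect.

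- The baseline check rejected in 83–85% of trials.
- The same test on the model residuals rejected in 4–5%, its nominal rate.
- The factorial ANOVA main effect rejected in 4.5–5.4%, also nominal.

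The baseline check fails here although the ANOVA it guards is valid.

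**Step 3. What if within-arm signed rank tests were then used to judge efficacy?** Again there is no treatment effect, with 17 per arm and an assumed SD of change of 0.25.

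- No common change: three active arms tested at 5% each give 1 − 0.95³ = 14% with at least one significant. The simulation gives 13%.
- A common fall of 0.1 to 0.2 in every arm: at least one active arm is significant in 67% to over 99% of trials. At least one active arm is significant while placebo is not in 16–46%.

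**The case against.** **Entry does not bound every baseline value.** A reader might infer that the entry range makes baseline HbA1c fail a normality test by design, or that the primary outcome would usually be diverted. The documents do not support either. The 5.7–6.4% window is one of several routes, and the IFG, IGT and AUSDRISK routes carry no HbA1c limit. The Participant recruitment section and Table 1 show screening by telephone and mail, with the first trial blood sample at the baseline visit. On that reading the qualifying value may be an older one and the analysed baseline a fresh measurement, which brings rejection down to 4–19% at N = 80. Method/design speaks of screening at two sites, so the reading is not certain. This objection stands, and the high rejection rates are conditional.

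**The text can be read more kindly.** The distribution in the choice rule could mean that of the outcomes, and the two-way ANOVA sentence could be taken to apply whatever the check shows. Then it goes too far to say that the plan would abandon the factorial analysis. But the only check named is on baseline data, and the kinder reading leaves the signed rank test without a defined role. What remains is an ambiguity about the primary test.

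**Looking at pooled baseline data does not by itself bias a randomised comparison.** This is true. The harm lies in a check that does not bear on the model and in the test it leads to.

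**Detail belongs in a SAP.** Residual diagnostics, transformations and sensitivity analyses commonly do, and their absence here is no finding. The point concerns a rule that the article states.

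**Conclusion.** The point holds as a fault in a stated rule. The check examines baseline data although the models need roughly normal outcome residuals. The named fallback cannot deliver the four-group comparison, the main effects or the interaction. The text leaves open which analysis governs HbA1c if the check fails. None of this depends on simulation.

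The chance of diversion is unknown. It runs from about 4% to over 90%, according to the mix of entry routes, the parent SD, whether the entry value is also the analysed baseline, and whether the test is pooled or by arm. The window can raise the chance of failure but need not.

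The false-positive figures in Step 3 show what within-arm testing would do under an assumed SD of change of 0.25 and an assumed common fall. They are not the error rate of this trial, since the article does not say that efficacy would be judged arm by arm. The sample size is untouched. The change is worth making before analysis: the Trial status section reports 38 completers with recruitment still open.

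**What to change.** 1. Remove the baseline normality check as a gate on the analysis. Baseline histograms may stay as description.
2. Fix the primary analysis in advance, whatever the distribution: a two-factor ANCOVA of week-12 HbA1c on baseline HbA1c, curcumin (yes/no), fish oil (yes/no) and their interaction. State that each main effect is averaged over the levels of the other factor, because with an interaction in the model the usual 0/1 coding gives effects against double placebo instead.
3. Inspect the residuals of that model.
4. Replace the signed rank test with a between-group sensitivity analysis that keeps the factorial structure, such as robust or bootstrap intervals or a rank-based factorial method.
5. Decide before unblinding which secondary markers, if any, are analysed on the log scale. The documents give no distributions from which to fix a list, so the choice is the sponsor's.

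The cost is about two sentences in the Data analysis section, with further detail in the SAP if there is one, and results reported as ratios for any log-transformed marker. Recruitment, visits and sample size do not change.

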### Interim visit

Participants are scheduled for the interim visit after 6 weeks of the intervention period (Table 1). They will need to provide completed diet and physical activity questionnaires. Compliance for the intervention is measured by capsule count and capsule log sheet. The follow-up visit includes only a 10-h overnight fast and anthropometric assessments using bioelectric impedance. Any adverse events or reports of difficulties in compliance with the intervention are recorded during this visit.

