### Post-intervention visit

The post-intervention visit is scheduled on the last day of the participant’s intervention period (Table 1). All baseline measures, including a 10-h overnight fast, anthropometric measurements and blood sample collection will be repeated on this visit. They will also be asked to fill out 3-day food record and physical activity questionnaires. Participants are advised to return capsule containers along with the capsule log sheet on the final visit day.

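### Baseline HbA1c is a covariate in neither the two-way ANOVA nor the ANCOVA, and the ANCOVA covariates are not limited to baseline values: a valid analysis that gives up precision

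*Protocol article*

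**What the plan says.** All references are to the protocol article.

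- **Outcome.** Primary outcome compares the four arms on the difference in HbA1c; the sentence runs to the "double active groups from baseline to the post-intervention visit". The measurement is available at both times: "HbA1c is measured in blood samples obtained at baseline and post-intervention visits".
- **Treatment test.** Data analysis states: "Two-way ANOVA with post hoc comparisons (Bonferroni correction) will be used to determine the effect of intervention on different variables". The same sentence gives this ANOVA the assessment of synergy. No covariate is named.
- **Adjusted model.** The next sentence reads: "ANCOVA will be used to assess the effects of confounding factors on treatment that include age, gender, BMI, physical activity levels and dietary intake". Baseline HbA1c is not in the list, and no visit is given for BMI, activity or diet.
- **Timing of those covariates.** Body composition, which includes BMI: "These parameters are measured in a fasting state at baseline, follow-up and post-intervention visits". Questionnaires, on diet: "They will be asked to complete a 3-day food record during each visit". Interim visit (week 6): "They will need to provide completed diet and physical activity questionnaires". Post-intervention visit (week 12): "They will also be asked to fill out 3-day food record and physical activity questionnaires".
- **Planning figures.** Sample size calculation uses an SD of 0.5 HbA1c units, a fall of 0.5 units, alpha 0.05, 80% power and 17 per group, raised to 20 for dropout. It does not say whether 0.5 is the SD of a single measurement or of a change.

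**The concern.** The baseline value of the outcome is the natural covariate in a small trial with a continuous endpoint measured before and after treatment. Here it is collected, yet it is absent from both models while five other variables are listed.

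Entry is possible through fasting glucose, OGTT, HbA1c or a risk score alone, so baseline HbA1c may vary considerably. The Randomisation section describes blocks of 8 intended to balance men and women and mentions no balancing on HbA1c. With 17 to 20 per arm, chance differences at baseline are to be expected. What is at stake is precision, and how far the estimate depends on such a difference.

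The second part concerns bias. BMI, diet and activity each have week-6 and week-12 values. A model that conditions on values recorded after treatment has begun can remove part of a treatment effect or introduce a spurious one. The text does not rule this out.

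**Working it through.** **Inputs.** From Sample size calculation: SD 0.5, difference 0.5, 17 per group, alpha 0.05 (two-sided assumed). Assumed, because the document does not give it: r, the correlation between baseline and week-12 HbA1c, from 0.3 to 0.9, with equal SDs at the two visits.

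**Step 1: reproduce the plan's figure.** A two-sample t-test with difference 0.5 and SD 0.5 has power 78.1% at 16 per group and 80.7% at 17. The stated 17 is right. Allowing for dropout, 17/(1 − 0.15) = 20. No stated figure is in dispute.

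**Step 2: variance.** Let σ be the single-visit SD.

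- Change score: variance 2σ²(1 − r).
- Baseline-adjusted: residual variance σ²(1 − r²).
- Ratio, adjusted to change score: (1 − r²)/[2(1 − r)] = (1 + r)/2.

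The ratio is below 1 for every r below 1, so the direction of the gain does not depend on the assumed r. Only its size does.

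**Step 3: pairwise power at 17 per group for 0.5 units.** The t-test uses 32 degrees of freedom for the change score and 31 for the adjusted model. If 0.5 is the single-visit SD, the two SDs are 0.5√[2(1 − r)] and 0.5√(1 − r²). If 0.5 is the SD of change, the adjusted SD is 0.5√[(1 + r)/2].

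| r | Variance ratio | 0.5 = single-visit SD: change → adjusted | 0.5 = SD of change: change → adjusted |
|---|---|---|---|
| 0.3 | 0.65 | 66.6% → 84.1% | 80.7% → 93.8% |
| 0.5 | 0.75 | 80.7% → 90.3% | 80.7% → 90.3% |
| 0.7 | 0.85 | 95.4% → 97.7% | 80.7% → 86.5% |
| 0.8 | 0.90 | 99.4% → 99.7% | 80.7% → 84.5% |
| 0.9 | 0.95 | about 100% for both | 80.7% → 82.6% |

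**Step 4: main effects.** These compare two arms with two arms, 34 against 34 completers. With 0.5 as the single-visit SD, the unadjusted change score already has about 93% power at r = 0.3 and 98% at r = 0.5. Low power is therefore at most an issue for pairwise contrasts.

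**Step 5: chance imbalance.** Suppose two arms differ by d at baseline. Week-12 means are then expected to differ by the treatment effect plus r·d. Subtracting baseline gives the treatment effect plus r·d − d, that is, the effect minus (1 − r)d. With a single-visit SD of 0.5, one standard error of d is 0.5√(2/17) = 0.17 (0.16 at 20 per arm). An imbalance of that size shifts the change-score contrast by 0.7 × 0.17 = 0.12 units at r = 0.3, 0.09 at r = 0.5 and 0.02 at r = 0.9, against a target of 0.5. Averaged over randomisations the shift is zero.

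**Step 6: which covariate values.** Data analysis names BMI, activity and diet without a visit. Questionnaires presents the repeat diet records as a way to detect changes during the trial. Strengths and limitation of study design links the on-trial diet and activity pattern to confounding, as the ANCOVA sentence does for its covariates. Use of follow-up values is therefore a realistic reading, but it is not stated.

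**The case against.** The strongest reply is that baseline is already used. The endpoint is a change, so baseline enters by subtraction, and a two-way ANOVA of change in a randomised trial is valid. This stands: a reader who infers that the primary analysis ignores baseline, or is biased, goes further than the document allows. Subtraction is not the same as adjustment, however. It fixes the slope at 1, loses precision for any r below 1 and over-corrects a chance imbalance.

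A reader might also infer that the trial is underpowered, from the 66.6% at r = 0.3. That figure needs a low assumed r together with 0.5 read as a single-visit SD, and it concerns a pairwise contrast. The document supports neither assumption. If baseline HbA1c strongly predicts week-12 HbA1c, as one would hope, the saving over a change score is modest: 15% of variance at r = 0.7 and 10% at r = 0.8.

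A third tempting reading is that the two models compete, with no rule for which one decides. The wording gives them different roles: the ANOVA determines the intervention effect, and the ANCOVA examines the other factors.

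Finally, the covariate list is introduced as what the factors include, so it may not be exhaustive, and the choice of visit could be settled in a document not shown. Both are fair. The article itself names the models and their covariates, though, and the variable left unnamed is the baseline of the primary outcome. Calling the covariates confounders is a matter of terminology and carries no weight here.

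**Conclusion.** The point holds as an improvement that costs almost nothing; it does not show an error in the planned test. Baseline HbA1c is in neither named model. Adding it lowers the variance of the treatment contrast by 35% at r = 0.3, falling to 5% at r = 0.9. The gain in pairwise power runs from negligible to about 17 percentage points (66.6% to 84.1%), depending on r and on what the 0.5 SD measures, neither of which the document settles. The sample size needs no change.

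The covariate-timing part is conditional. The plan does not say that on-treatment BMI, diet or activity will be used, only that these are collected and are not excluded. If they were used, the adjusted effect could be biased by an amount that cannot be calculated from the document.

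**What to change.** - **Primary model.** A two-factor ANCOVA of week-12 HbA1c (or of change, which gives the same treatment estimate once baseline is in the model) on curcumin, LCn-3PUFA, their interaction and baseline HbA1c. Add sex, which the blocking is meant to balance.
- **Secondary outcomes.** The same model with the matching baseline value of each outcome.
- **Supportive ANCOVA.** Age, BMI, physical activity and diet as recorded at baseline only.
- **On-trial diet, activity and weight.** Report changes by arm descriptively and do not enter them as covariates.

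The cost is a few sentences of analysis text and one or two degrees of freedom. Every value is already collected. Trial status reports recruitment still under way with 38 completers, so the wording could be settled before any unblinded analysis.
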